### Statistical analyses plan

To ensure the integrity and internal validity of the study, participants will be explicitly instructed not to participate in any other communication-related training during the study period. Additionally, participants will be asked to refrain from discussing the VR training content with colleagues who may also be involved in the study. Clear communication regarding these expectations will help minimize potential sources of bias or contamination.

### Primary analysis

The main objective of the analysis is to evaluate the pedagogical effectiveness of the VR training program. This will be assessed through the comparison of knowledge quiz scores completed after each scenario (Score 1 and Score 2). The mean difference between these two scores will be calculated for each participant. A paired-sample t-test will be used to determine whether the change in knowledge is statistically significant, with a significance level set at *p* < 0.05.

This test is appropriate for the within-subjects design, where each participant serves as their own control.

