### Design and setting

This study adopts a single-arm, pre-post design to evaluate the usability, user satisfaction, self-perceived competence, and knowledge acquisition related to a virtual reality (VR) training program aimed at enhancing verbal and nonverbal communication skills among healthcare professionals working in a Parisian academic geriatric hospital.

All participants will undergo the same immersive VR-based training intervention. The impact of the training will be assessed by comparing each participant’s outcomes before and after the intervention, focusing specifically on self-perceived competence and knowledge acquisition related to the management of disruptive behavioral and psychological symptoms of dementia (BPSD). This design was selected due to feasibility constraints, including limited staff availability and the exploratory, educational nature of the intervention. Although no comparator group is included, the within-subject approach allows each participant to serve as their own control, thus enabling a rigorous and individualized assessment of training impact. This exploratory study is expected to provide valuable insights into the practical feasibility and pedagogical value of immersive VR training in geriatric care settings.

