### Protocol workflow

#### Step one: scenario design phase.

In this phase, 10 healthcare professionals (out of 50 participants) who have given written consent to participate in the study, will be invited to a focus group. The researchers (a couple of 2 psychologists and 2 geriatricians) will provide them two scenarios, each describing a clinical context involving a patient with disruptive BPSD (aggression, opposition, agitation, and/or anxiety) and a professional caregiver (example of a scenario in S2 Text). The scenarios will be written in a precise but concise manner, outlining situations where conflicts are likely to arise due to the patient’s non-cooperative behavior towards the caregiver (*e.g*., grooming with an unwilling patient or agitation during group activities).

Participants will be asked to provide feedback on the scenarios based on their own professional experience and knowledge, as well as to suggest modifications or additions to the dialogues and gestures of the fictional characters in order to either aggravate the conflict or soothe the patient, depending on the situation. To guarantee the pedagogical excellence of the scenarios, we will ensure that the experiences and knowledge of investigators, including doctors and psychologists, as well as healthcare personal involved in the focus group, are incorporated. Moreover, recommendations from health authorities and healthcare societies regarding the care of patients experiencing behavioral and psychological symptoms of dementia (BPSD) will also be taken into consideration. By doing so, the scenarios can be co-written with a well-rounded and comprehensive approach, taking into account various perspectives and expertise, thus ensuring their accuracy and effectiveness.

To evaluate later the pedagogical value of the scenarios, participants will be asked to propose multiple choice questions. These quizzes will be used to evaluate the subsequent participants for their ability to identify appropriate and inappropriate verbal and nonverbal communication by the fictional healthcare professional, as well as their knowledge about optimal ways to behave with demented patients with disruptive BPSD, as represented by the fictional patient in the scenarios.

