#### Step three: virtual reality training and evaluation.

Following informed consent, the 40 healthcare professionals not involved in the scenario co-design focus group will participate in a single-arm, pre-post study evaluating the effectiveness of a VR-based communication training program.

Each participant will attend one individual single-session lasting approximately 2 hours, scheduled within a 10-day period. Two sessions will be held each day (9:30–11:30 am and 2:00–4:00 pm), ensuring participant availability across day and night shifts.

At the start of the session, participants will complete the “Verbal and Nonverbal Communication Training Needs Questionnaire” (see S3 Text) to assess their self-perceived communication challenges related to the management of patients with behavioral and psychological symptoms of dementia (BPSD).

They will then proceed to view the first immersive VR scenario using a 3D headset, based on content co-developed during the scenario co-design phase. Immediately afterward, they will complete a multiple-choice quiz evaluating their understanding of verbal and nonverbal communication strategies illustrated in the scenario.

A debriefing session with psychologist investigators will follow, to discuss the participant’s quiz responses and provide tailored feedback.

Participants will then access a reinforcement module on Moodle, designed to consolidate the key theoretical concepts presented in the first scenario.

This sequence (VR viewing → quiz → debriefing → Moodle training) will be repeated for a second VR scenario, followed again by a debriefing and Moodle reinforcement.

At the end of the training session, participants will complete the post-training assessments, including:

satisfaction with the training experience,perceived competence in managing BPSD,and perceived pedagogical effectiveness of the VR scenarios.

The full process is presented in Fig 3.

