#### Step four: assessments.

After each VR scenario, participants will complete a multiple-choice quiz to assess their knowledge of appropriate verbal and nonverbal communication strategies with patients suffering from BPSD. The quiz scores, based on the percentage of correct responses, will be calculated separately for Scenario 1 and Scenario 2. These scores will be returned to participants to help track their progress and knowledge acquisition.

The primary outcome of the study, the pedagogical effectiveness of the training, will be measured by the improvement in participants’ knowledge scores between Scenario 1 and Scenario 2 (see calculation method in the *Data collection and assessment tools* section).

Participants will also complete questionnaires evaluating:

their overall satisfaction with the training method (VR scenario movies and Moodle reinforcement),their self-perceived level of competence.

In addition, they will complete two supplementary questionnaires:

one assessing satisfaction with the VR scenarios, andanother evaluating the usability of the 3D VR training method (see details in *Data collection and assessment tools*).

The total time required to complete all assessments will not exceed 1 hour.

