#### The evaluation of the participant’s satisfaction of the two VR scenarios.

All participants will be asked to complete a scenario-specific satisfaction questionnaire, developed by the research team (see S4 Text), to assess their experience with each of the two immersive VR scenarios.

This questionnaire will gather feedback on elements such as:

the realism and relevance of the scenarios,the emotional engagement generated by the immersive content,and the perceived usefulness of the scenarios in improving real-life communication with patients with BPSD.

**To assess the usability of the VR 3D training method**, the System Usability Scale (SUS) will be employed [47]. The SUS provides a subjective viewpoint of the user on the system and its ease of use on a 5-point Likert-type scale ranging from 1 to 5. The total is calculated using the SUS questionnaire and ranges from 0 to 100, with a higher score indicating greater usability satisfaction [47].

**The learners’ self-perceived level of competence** will be quantitatively analyzed using a questionnaire created by the researchers (see S5 Text) which is based on the “perceived competence” section of the “Intrinsic Motivation Inventory” [48]. This subsection evaluates motivation and competence in a multidimensional way. The results will be reported on a 5-point Likert-type scale, ranging from 1 to 5. A higher total score indicates a greater sense of acquired competence.

**The evaluation of the pedagogical effectiveness of the training will be based on** the participants’ The pedagogical effectiveness of the training will be assessed by measuring participants’ knowledge progression between Scenario 1 and Scenario 2 of the immersive VR training. After viewing each scenario, participants will complete a multiple-choice quiz, and the learning platform will automatically calculate their scores:

Score 1 after Scenario 1,Score 2 after Scenario 2.

The difference between Score 2 and Score 1 will be used as an indicator of knowledge acquisition:

If Score 2 ≤ Score 1, no learning progress is observed,If Score 2 > Score 1, the participant is considered to have improved in knowledge and understanding of appropriate communication strategies.

This within-subject comparison provides a direct measure of the training tool’s educational value and its effectiveness in reinforcing verbal and nonverbal communication skills relevant to the management of patients with disruptive BPSD.

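### The primary comparison subtracts scores on two different quizzes taken in one fixed order, so a gap in quiz difficulty cannot be told apart from learning

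*Protocol article*

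**What the plan says.** Under Step three, each participant watches one film and then takes a quiz "evaluating their understanding of verbal and nonverbal communication strategies illustrated in the scenario". Debriefing and a Moodle module follow. The whole sequence "will be repeated for a second VR scenario, followed again by a debriefing and Moodle reinforcement". Step four has the scores expressed as percentage correct; they "will be calculated separately for Scenario 1 and Scenario 2", and the improvement from one to the other is the primary outcome.

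On order, Step three says "They will then proceed to view the first immersive VR scenario using a 3D headset", and Design and setting says "All participants will undergo the same immersive VR-based training intervention". No sequence groups are described. On the origin of the items, Step one says that, in the focus group, "participants will be asked to propose multiple choice questions".

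Primary analysis gives the comparison: "This will be assessed through the comparison of knowledge quiz scores completed after each scenario (Score 1 and Score 2". The test is a paired t-test at the 5% level, justified by each participant acting as their own control. Data collection and assessment tools adds the reading rule: a Score 2 above Score 1 counts as improved knowledge, and anything else as no progress. It then claims: "This within-subject comparison provides a direct measure of the training" tool's educational value.

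**The concern.** A paired difference measures change in a person only if the same measure, or an interchangeable one, is used both times. Here the two scores come from quizzes tied to different films. The items are newly written by a focus group, so their difficulty is unknown. Using participants as their own controls removes differences between people; it does nothing about differences between instruments.

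With one order for everyone, time and quiz coincide: first always means quiz 1 and second always means quiz 2. Learning and quiz difficulty are then perfectly confounded, and no model fitted afterwards can separate them. The reading rule nevertheless assigns the whole difference to learning.

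The error can go either way. If quiz 2 happens to be easier, the training may be declared effective without any learning. If it is harder, a real gain may be missed. This is the study's only primary test, and the Abstract hypothesises a significant improvement.

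**Working it through.** **Inputs from the article (Sample size justification).** Two-sided paired t-test, 5% level, standardised effect dz = 0.5, 80% power, minimum 34 participants, 40 planned.

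**Inputs assumed.** The article gives no SD of the difference, number of items or quiz difficulty. I take an SD of 15 percentage points (range 12 to 20) and a difficulty gap of 5 points (range 1 to 7.5). Five points would be half an item on a 10-item quiz.

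**Step 1. Reproduce the article's figure.** Power comes from the noncentral t distribution with n − 1 degrees of freedom and noncentrality dz × √n.
- n = 33: power 0.795
- n = 34: power 0.808, the first n to reach 0.80
- n = 40: noncentrality 0.5 × √40 = 3.16, power 0.869

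The stated minimum of 34 is correct. The fault lies in what is compared, not in the sample size arithmetic.

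**Step 2. What the test estimates.** Let L be mean learning and g the amount by which quiz 2 is easier than quiz 1. Under the fixed order, the expected value of Score 2 − Score 1 is L + g. The test is of L + g = 0, with noncentrality (L + g)/SD × √40.

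**Step 3. No learning (L = 0), quiz 2 easier, n = 40.** The nominal rate is 5%.

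| Gap g | SD | g/SD | Noncentrality | P(p < 0.05) |
|---|---|---|---|---|
| 1 | 15 | 0.067 | 0.42 | 7% |
| 2 | 15 | 0.133 | 0.84 | 13% |
| 5 | 20 | 0.250 | 1.58 | 34% |
| 5 | 15 | 0.333 | 2.11 | 54% |
| 5 | 12 | 0.417 | 2.64 | 73% |
| 7.5 | 15 | 0.500 | 3.16 | 87% |

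The same point can be made without assuming a scale in points. A gap of 0.2 SD gives a significant improvement with probability 0.234, against 0.025 in that direction. At n = 34 the figure is 0.204, so a larger sample makes the problem worse.

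**Step 4. Real learning, quiz 2 harder.** At SD 15, dz = 0.5 is a gain of 7.5 points. With quiz 2 harder by 5 points, the net is 7.5 − 5 = 2.5 points, 2.5/15 = 0.167 SD, noncentrality 1.05. Power falls from 87% to 18%.

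**Step 5. Both orders used, 20 participants each.** Call the films A and B, and let g be the ease of quiz B relative to quiz A.
- A then B: expected change L + g
- B then A: expected change L − g
- Mean of the two: [(L + g) + (L − g)]/2 = L

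The gap cancels. With the SD pooled within order, the standard error is SD/√40 on 38 degrees of freedom. Power at dz = 0.5 is 0.869, and 0.807 if only 34 participants complete (17 per order). A simulation of 20,000 runs (SD 15, gap 5) gave false positives of about 5% under this design, against 53.7% under the fixed order, and about 87% power for a 7.5-point gain.

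**The case against.** **The premises are partly inferred.** The article never says outright that the items differ or that the quizzes are not equated. The items are still to be written, some could be common to both quizzes, and the full protocol may describe matching. This stands as a caution on wording. But Step three ties each quiz to the film just seen, and the article itself calls the raw difference a direct measure of educational value, which is unsupported as described. Fixed order is likewise the natural reading rather than an explicit statement: the text gives one sequence, one arm and no alternative.

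**The limitation is acknowledged.** Limitations of the study design admits that, without a control group, other factors could explain the result, and the study is called exploratory. That caveat is general. It does not mention quiz or scenario difficulty, and this problem can be solved without a control group.

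**The size is assumed.** This is true. No document evidence shows which gap is plausible, and a 1-point gap barely matters (7%). A 2-point gap already gives 13%.

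**The remedy is incomplete.** This is also true. Changing the order cancels an additive difficulty gap only. Familiarity with the quiz format or headset would still count as learning: a 5-point practice effect at SD 15 would be significant 54% of the time under the revised analysis too. Nor does it resolve a separate mismatch: the Abstract promises pre- and post-training scores, yet Score 1 follows the first film and Score 2 precedes the second debriefing and Moodle module.

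**Conclusion.** The concern holds. As the article describes it, the primary comparison estimates learning plus the difference in quiz difficulty, and the planned data cannot separate them. The error rate for a claim of learning is therefore uncontrolled. With 40 participants and an SD of 15 points, the false-positive rate runs from 7% at a 1-point gap to 54% at 5 points and 87% at 7.5 points. In the other direction, a 5-point gap cuts power from 87% to 18%. These sizes depend on the assumed SD and gap; the confounding does not. It rests on scenario-specific quizzes, a single order and the absence of any stated equating. The sample size of 34, raised to 40, is arithmetically correct but gives no protection. The point should be settled before data collection, because it cannot be repaired afterwards.

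**What to change.** Randomise the order of the two scenarios: 20 participants take A then B and 20 take B then A, each film keeping its own quiz, debriefing and Moodle module. Replace the plain paired t-test with a model for quiz score that has terms for period (first or second) and scenario and a random participant effect. With complete pairs, this amounts to averaging the two order-specific mean changes with equal weight, with the standard error pooled within order (38 degrees of freedom when all 40 complete). Report the change from first to second with its 95% confidence interval. Withdraw the claim that the raw difference measures educational value directly, and state that practice effects remain part of the estimate. If the full protocol already equates the quizzes, say how in the article.

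The cost is a 40-line allocation list, loading the films in either order, a revised analysis sentence and one degree of freedom. No participants, visits or quiz items are added. Management of study amendments and termination requires ethics board approval first. Status and timeline puts data collection in September to December 2025, after the article's publication in June 2025, so the plan left time for it.

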### Secondary analyses

Additional outcomes will be explored using both descriptive and inferential statistical methods.

Participant satisfaction with the training program will be summarized using means and standard deviations, and further examined through frequency distributions of Likert scale responses.Changes in self-perceived competence before and after training will be analyzed using a paired-sample *t-*test. If normality assumptions are not met, a non-parametric alternative such as the Wilcoxon signed-rank test will be applied.Descriptive analyses will also be performed for system usability and scenario-specific satisfaction. Potential associations between these outcomes and participant characteristics (e.g., age, professional role, years of experience) will be assessed using correlation analyses or regression models, where appropriate.Additionally, exploratory subgroup analyses may be conducted to identify whether training outcomes vary according to specific participant factors, including professional role or prior exposure to virtual reality training. Predictive modeling using regression techniques may be applied if supported by the data.

### Handling missing data

Analyses will be conducted on a per-protocol basis. Participants who do not complete the post-training assessments (e.g., knowledge quizzes or self-perception questionnaires) will be excluded from the final analysis, and no imputation will be applied for missing data. Data completeness will be monitored throughout the study, and sensitivity analyses may be conducted if the extent of missing data is deemed substantial. Given the one-time, on-site nature of the intervention, participant dropout is expected to be minimal. Attendance will be recorded at the start of the session. Should a participant begin the session but fail to complete the post-training assessments, no additional data will be collected and their dataset will not be included in the analysis. To promote retention and minimize incomplete data, efforts will be made to ensure participant understanding and comfort prior to the start of the training.

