**Fig 1 pone.0325910.g001:**
[figure not shown]
SPIRIT schedule of enrolment, intervention, and assessments.

This sample size exceeds the minimum required number of 34 participants, as determined by an a priori power analysis (for a moderate effect size, dz = 0.5, with 80% power at a 5% significance level), and was increased slightly to account for potential dropouts or missing data.

Participants will be recruited on a voluntary basis via posters in the geriatric wards or during staff meetings. There will be no restrictions regarding age or gender. Healthcare professionals with a history of epilepsy, pregnant individuals, or those prone to motion sickness, balance problems, or migraines will be excluded. Both day and night shift staff are eligible.

Participants may discontinue the training session at any time, particularly in the event of discomfort, cybersickness, or any adverse reaction to the immersive VR environment. No modification of the training content is planned during the session. In case of early withdrawal, participants’ data will be excluded from the final analysis.

Data will be anonymized and will not impact any professional evaluations. No financial compensation will be provided. Psychologist evaluators will have no prior professional relationship with the participants. Each of the 40 participants in the main study will complete pre- and post-training assessments surrounding a 2-hour VR training session

We will ensure participants are available for focus groups, training, and evaluations. Total participation time will not exceed 120 minutes, including approximately 60 minutes for immersive virtual reality scenario viewing, quizzes, debriefing, and Moodle-based reinforcement, and 60 minutes for the completion of pre- and post-training questionnaires and evaluation forms (Fig 2). sample).

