### Sample size justification

The sample size was determined based on an a priori power analysis for a paired-sample design. To detect a moderate effect size (Cohen’s dz = 0.5) with 80% power at a 5% significance level using a two-tailed paired t-test, a minimum of 34 participants was required. To allow for potential dropouts or incomplete data, we increased the sample size to 40 participants. The calculation was performed using G*Power (version 3.1). We plan to include 40 participants, allowing for possible attrition.

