### Safety considerations

To ensure the safety of participants in this study, potential risks have been identified and addressed. Exposure to virtual reality, as indicated by the 2019 French National Health Security Agency (ANSES) survey, may disrupt the sensory system and cause symptoms such as nausea, dizziness, sweating, paleness, loss of balance, collectively known as “*cyber kinetosis*” [49]. These symptoms may manifest in sensitive individuals within minutes of use, and may also temporarily affect sensory, motor, and perceptive abilities, altering manual dexterity or body orientation. They also include the feeling of motion sickness or of nausea and dizziness caused by virtual reality experiences or other types of immersive technologies. Additionally, exposure to flashing lights emitted by LED screens can trigger epileptic seizures in individuals with a predisposition to them [49].

To minimize the risk of these effects, ANSES’ recommendations will be followed during this study:

Testing with the virtual reality device will be immediately halted if participants experience symptoms such as nausea, dizziness, sweating, or paleness.Each participant will observe a rest period of 15 minutes during and after use of the virtual reality device.Participants with epilepsy or who are sensitive to motion sickness, balance issues, migraines, or pregnant women will not be included in the study (as stated in the information letter and exclusion criteria).

All adverse events related to the virtual reality training, whether solicited or spontaneously reported, will be documented by the research team using a standardized reporting form. This includes any symptoms of cybersickness (e.g., dizziness, nausea), emotional discomfort, or unexpected stress reactions during or after the sessions. The principal investigator will be responsible for reviewing and assessing all reported events in terms of severity, duration, and possible relationship to the intervention. Any serious or unexpected adverse events will be promptly reported to the institutional ethics committee in accordance with AP-HP procedures. Participants will be explicitly informed that they can report any discomfort at any time and may discontinue the session without consequence.

In the unlikely event of harm related to participation, appropriate support will be provided in accordance with institutional policies.

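### Excluding everyone who stops early or misses a post-training form leaves satisfaction and usability described mainly in people who tolerated VR, and can discard valid primary-outcome pairs

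*Protocol article*

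**What the plan says.** The rule appears in two sections of the protocol article.

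- **Handling missing data** sets the analysis population: "Analyses will be conducted on a per-protocol basis". It continues: "Participants who do not complete the post-training assessments (e.g., knowledge quizzes or self-perception questionnaires) will be excluded from the final analysis", with no imputation. For a person who begins the session but does not finish the post-training assessments, "no additional data will be collected and their dataset will not be included in the analysis".
- **Participants, sampling plan, inclusion, and exclusion criteria** says that after early withdrawal a participant's "data will be excluded from the final analysis". The same paragraph gives discomfort, cybersickness and adverse reaction to the VR environment as the particular reasons for stopping.

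The **Safety considerations** section adds: "Testing with the virtual reality device will be immediately halted if participants experience symptoms such as nausea, dizziness, sweating, or paleness". It also has all VR-related adverse events documented on a standard form.

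Overall satisfaction is rated once, at the end of the session. The primary analysis is a paired t-test on Score 1 and Score 2, the two quiz scores. Satisfaction and SUS are secondary and are summarised descriptively. The missing-data section also says that attendance is recorded at the start, that dropout should be minimal, and that sensitivity analyses may be done if missing data are judged substantial. It gives no threshold or method for these.

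**The concern.** There are two separate problems.

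**Selection.** People made unwell by the headset are the most likely to stop. Those who stop are either never asked for a rating or have their rating left out. Satisfaction and usability are partly judgements on that same experience, so the chance of being in the analysis is plausibly related to the rating itself. The means would then answer how completers rated the programme, not how those who tried it rated it. User satisfaction is in the study title and usability is a stated aim, so readers will take these figures as describing the programme among staff offered it.

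**Loss of usable primary data.** The primary comparison needs only Score 1 and Score 2. The exclusion rule, with its list of quizzes or self-perception questionnaires, removes a participant with both scores if a later form is missing. Nothing in the analysis requires that.

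**Working it through.** **1. The plan's own sample size.** Inputs from the Sample size justification section: "To detect a moderate effect size (Cohen’s dz = 0.5) with 80% power at a 5% significance level using a two-tailed paired t-test", for which "a minimum of 34 participants was required". Using exact noncentral-t power with df = n − 1 and noncentrality 0.5 × √n:

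| n analysed | Power |
|---|---|
| 33 | 0.795 |
| 34 | 0.808 |
| 36 | 0.831 |
| 38 | 0.851 |
| 40 | 0.869 |

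The minimum of 34 is reproduced. The section then says: "To allow for potential dropouts or incomplete data, we increased the sample size to 40 participants". The margin is 40 − 34 = 6, or 6/40 = 15%. If all six are lost, power is still about 81%. Power is not the main problem.

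**2. Bias in a completers-only mean.** Let k of 40 starters be excluded, with completers' mean C and excluded participants' mean E (what they would have scored).

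All-starters mean = [(40 − k) × C + k × E] / 40

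Bias = C − all-starters mean = (k/40) × (C − E)

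The protocol gives neither k nor the gap C − E. Both are assumptions here; k = 6 is the plan's whole margin for dropout and incomplete data combined.

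| Excluded (k) | Share | SUS bias, gap 10 | gap 25 | gap 35 | gap 40 |
|---|---|---|---|---|---|
| 0 | 0 | 0 | 0 | 0 | 0 |
| 2 | 0.05 | 0.5 | 1.25 | 1.75 | 2.0 |
| 4 | 0.10 | 1.0 | 2.5 | 3.5 | 4.0 |
| 6 | 0.15 | 1.5 | 3.75 | 5.25 | 6.0 |

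Worked example: if completers average 75 and those excluded would score 50 (k = 2) or 40 (k = 6), the all-starters means are (38 × 75 + 2 × 50)/40 = 73.75 and (34 × 75 + 6 × 40)/40 = 69.75. The overstatement is 1.25 and 5.25 points on the 0 to 100 scale.

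For the 1 to 5 satisfaction rating, with assumed gaps of 0.5 to 3, the bias is 0.03 to 0.15 at k = 2 and 0.08 to 0.45 at k = 6.

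**3. Completion.** Over all starters, with exact 95% intervals, completion would be 38/40 = 95% (83% to 99%), 36/40 = 90% (76% to 97%) or 34/40 = 85% (70% to 94%). Inside the analysed set it is 100% by construction, so it has to be reported over starters to carry any information.

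**4. Primary outcome.** A person who stops before the second quiz has no Score 2 and drops out of any complete-case paired test, whatever the rule. The avoidable loss is limited to people with both scores who lack a later form. The document gives no basis for estimating how many.

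**The case against.** The case for leaving the rule alone has real force.

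- **Few exclusions are likely.** People prone to motion sickness, balance problems or migraine, those with epilepsy, and pregnant individuals are not enrolled. The session is single, supervised and on site. With no exclusions the bias is zero. This stands, and it limits the expected size.
- **The direction is inferred.** Halting the headset is not the same as withdrawal, SUS measures ease of use and not symptoms, and a form missed for lack of time need not come from a dissatisfied participant. This stands in part: an upward bias is likely for symptom-driven stops and uncertain for other reasons.
- **Tolerability is still recorded.** A reader might infer that data on people who did badly are deleted. The protocol does not say so. It excludes them from the final analysis, while adverse event forms, the attendance record and the flow diagram keep the tolerability data and the number who started.
- **Feasibility.** A reader might also infer that feasibility will be overstated. The article defines no feasibility statistic and does not say it will be read from the per-protocol set, so that is not shown.
- **A sensitivity analysis is foreseen.** It is optional and unspecified, and it cannot recover ratings that were never requested. This does not answer the concern.
- **The outcomes are secondary and descriptive** in a self-described exploratory study, with no decision threshold attached. This bears on severity and does not remove the problem.

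**Conclusion.** The point holds as a should-fix. The exclusion rule is explicit, and the protocol's own account of why people stop ties exclusion to poor tolerance of VR. If such exclusions occur, the satisfaction and usability summaries will describe mainly people who tolerated the headset and will probably be too favourable.

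The size cannot be established from the document. The figure of about 1 to 5 SUS points assumes 2 to 6 exclusions and a gap of 25 to 35 points. Its upper end further treats the whole margin of six as people who would have rated VR poorly. Fewer exclusions or a smaller gap shrink it, to zero if nobody is excluded. A claim of certain, one-directional bias would go beyond what the text supports.

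For the primary analysis, the fault is the needless loss of valid score pairs when only a later questionnaire is missing. The number affected is unknown, and power stays at about 81% even at n = 34.

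**What to change.** Replace the blanket exclusion in both sections with outcome-specific analysis sets among all who start VR:

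1. **Primary:** everyone with both Score 1 and Score 2, whatever other forms are missing.
2. **Each questionnaire:** everyone who completed it, with the number of starters shown beside the number analysed.
3. **Early stoppers:** offer the SUS and satisfaction forms to those who are willing, and amend the sentence that ends data collection for them. The rule for halting VR is not affected.
4. **Reporting:** completion, early stopping with reasons, and cybersickness, each over all starters.
5. **Sensitivity:** keep the completers-only analysis in this role.

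The cost is a wording change and two short forms for a few people, with no extra participants. The figures may look slightly less favourable. The change should be made before data collection, which the article schedules for September to December 2025, because ratings not requested on the day are unlikely to be recoverable afterwards.
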